#### Enrollment in THRIVE

Enrollment in THRIVE begins with identification by CMs during hospitalization using a validated predictive algorithm developed by our team [31]. The algorithm is housed in the EHR and leverages principles of behavioral economics to “nudge” CMs to initiate a THRIVE referral. The THRIVE EHR flag was introduced to alleviate the need for CMs to manually identify THRIVE participants.

Once identified, THRIVE participants will receive a home care referral to Penn Medicine at home care services. The initial home care visit will be scheduled and completed by a nurse within 48 hours of discharge, at which time, medications are reconciled, discharge orders are reviewed, and person-centered goals of care are set. During the initial evaluation, home care nurses will determine the frequency of visits deemed necessary, with weekly visits ranging from 1 to 3 times depending on needs. Participants may receive additional services, such as speech or occupational therapy as required. All THRIVE participants receive a social work referral, their psychosocial needs are further assessed, and connections to community resources are provided. THRIVE participants receive a CHW referral as deemed necessary.

As a part of the THRIVE pathway, physician colleagues will extend continuity of care into the home following discharge to all THRIVE participants. Home care nurses will provide a brief patient status update to discharging physicians following the first home visit. During calls, nurses can raise questions about medications, clarify discharge orders, and receive guidance on emerging symptoms with the provider most recently involved with care. Extended supervision by discharging physicians will be provided for up to 30 days or until THRIVE participants have seen a primary care provider or specialist.

THRIVE participants will receive further support during discussions in our weekly interdisciplinary case management conferences for 4 weeks following discharge. During case management meetings, we will support connections to postacute primary, specialty care, behavioral health, and substance use services as needed. If a source of primary care is absent, we work to link THRIVE participants to community providers. Our intensive support addresses many of the social determinants of health that are known to influence health inequities such as housing, food insecurity, and limitations in access to behavioral health (Figure 1).

#### Implementation Strategies

We will use a series of implementation strategies to improve the effectiveness of THRIVE and promote its use [52]. These strategies will include (1) building and sustaining a coalition of diverse stakeholders through regular meetings and providing updates on THRIVE outcomes; (2) developing educational materials and conducting ongoing training of CMs, physicians, and advanced practice providers in the hospital and nurses and managers in home care using a scripted in-person training module to teach them about the elements of THRIVE and their role in implementing it; (3) auditing and providing feedback through the use of a referral dashboard to monitor all eligible THRIVE participants to document the individuals who were eligible for the intervention and not referred and providing feedback to case managers and document reasons for why referrals did not take place; (4) emailing reminders to case managers at weeks 2, 4, and 6; (5) identifying and preparing champions to promote the use of THRIVE; and (6) engaging of our advisory board to seek feedback for improvements.

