#### Randomization

Groups of case managers (4 in the first group, 4 in the second, and 5 in the third) were randomly assigned by the study methodologist to each sequence using a random number generator. A stepped wedge design—that is, a 1-time crossover design—was used for THRIVE (Table 2).

Specifically, following a baseline data collection period, 4 case managers will be randomized to receive training on the THRIVE clinical pathway. Following training, they begin referring to the THRIVE clinical pathway. At 8-week intervals, the remaining case managers will be trained in the THRIVE intervention and will be able to begin submitting referrals. Since case managers from the sequences work within the same space, the ability to conceal allocation was limited; however, all case managers were made aware of their upcoming ability to refer to the THRIVE clinical pathway.

**Table 2 table2:** Study design for the type 1 hybrid effectiveness-implementation stepped wedge cluster randomized controlled trial of the THRIVE clinical pathway.

Cluster	Baseline (3 months)	Enrollment period 1 (8 weeks)	Enrollment period 2 (8 weeks)	Enrollment period 3 (8 weeks)	Follow-up (18 months)
Sequence 1 (4 case managers)		✓	✓	✓	✓
Sequence 2 (4 case managers)			✓	✓	✓
Sequence 3 (5 case managers)				✓	✓

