### The THRIVE Intervention

#### Current Usual Care

To provide evidence of the effectiveness and implementation of THRIVE, we will compare individuals receiving THRIVE services to patients receiving usual care. The current usual care will serve as the control condition that patients will receive during the control phases of the design. Usual care may include discharge care planning that reflects the patient’s medical needs, which may or may not include referrals to home care, skilled nursing or rehabilitation facilities, and other outpatient services.

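### Only case managers have a randomised start; the flag, dashboard feedback, champions and shared staff training are not stated to be limited to crossed-over case managers, so control patients in periods 1 and 2 can be partly exposed

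*Protocol article*

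**What the plan says.** The Randomization section staggers case managers and no one else: "Groups of case managers (4 in the first group, 4 in the second, and 5 in the third) were randomly assigned", and "At 8-week intervals, the remaining case managers will be trained in the THRIVE intervention and will be able to begin submitting referrals". It adds: "Since case managers from the sequences work within the same space, the ability to conceal allocation was limited". All case managers also knew in advance that they would be able to refer.

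Other parts of THRIVE act through shared staff and systems:

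- Implementation Strategies lists "conducting ongoing training of CMs, physicians, and advanced practice providers in the hospital and nurses and managers in home care".
- The same list has "auditing and providing feedback through the use of a referral dashboard to monitor all eligible THRIVE participants", used to "document the individuals who were eligible for the intervention and not referred and providing feedback to case managers". It also has champions, and emailed reminders to case managers at weeks 2, 4 and 6.
- Enrollment in THRIVE says: "The THRIVE EHR flag was introduced to alleviate the need for CMs to manually identify THRIVE participants". The flag is meant to nudge case managers towards a THRIVE referral.

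None of these is given a start date or a link to a sequence.

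On the control condition, Current Usual Care says: "Usual care may include discharge care planning that reflects the patient’s medical needs, which may or may not include referrals to home care". Outcomes and Measures under Aim 1 names the home care referral rate as primary, compared with baseline and with case managers not yet crossed over. Table 3 instead defines the referral measure as THRIVE referrals among eligible patients. The Analysis section models use outcomes with fixed effects for time.

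**The concern.** A stepped wedge needs the control cells to stay free of the intervention. Here the randomised unit is one link in a chain that the whole hospital shares. To serve sequence 1's patients in period 1, discharging physicians and home care nurses must already be working in the THRIVE model, and the text ties none of them to a sequence. A case manager still in the control condition may see the flag, receive dashboard feedback, share a workspace with trained colleagues, or work with a trained physician. That case manager cannot submit a THRIVE referral but can order ordinary home care. Such an order counts towards the home care referral rate.

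At stake is bias towards no effect in the only two periods where treated and control case managers are observed side by side. The Strengths and Limitations section names only the single institution, and the article describes no safeguard against contamination.

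**Working it through.** **1. Where the randomised information sits (Table 2).** At baseline no sequence is treated. In period 1, sequence 1 is treated and sequences 2 and 3 are control. In period 2, sequences 1 and 2 are treated and sequence 3 is control. In period 3 and follow-up all are treated. Only periods 1 and 2 contain both conditions.

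**2. Effect of leakage on the estimate.** Let X = 1 in treated cells and 0 otherwise, θ the true effect, and c the share of θ that reaches control cells once step 1 has begun. In periods 1 and 2 the contribution of THRIVE to a cell mean is

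θ[X + c(1 − X)] = cθ + (1 − c)θX.

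The term cθ is the same for every sequence in the period, so the time effect absorbs it. The coefficient on X is (1 − c)θ. Baseline (all X = 0) and period 3 and follow-up (all X = 1) fit exactly with their own time effects and do not alter this. Weighted least squares on the cells (4, 4 and 5 case managers; a 13-week baseline and three 8-week periods) gives the same answer with and without sequence effects: 0.90, 0.80, 0.70 and 0.50 for c = 10%, 20%, 30% and 50%.

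In a log-link model such as the planned negative binomial, c is a share of the log rate ratio. A true ratio of 0.50 with c = 20% gives 0.50^0.8 = 0.57.

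**3. Illustration of size.** The documents give no c. The Background's 24% readmission figure and the pilot's 50% decrease are used only as examples; neither is stated as a planning value. The undiluted difference is 24% × 0.5 = 12 points.

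**4. Illustration of power.** The stated sizes are 472 (readmissions) and 534 (ED visits) for 80% power at the .05 level. The planning rates are not given, so these sizes cannot be reproduced from their own inputs. As an example, 24% against 12% needs 160 per group two-sided, not 236; since those rates are not claimed as planning rates, this shows no error. Taking the stated 80% as given, in a simple two-group approximation,

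power = Φ[(1.960 + 0.842)(1 − c) − 1.960].

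This gives the lower end of each power range below. The upper ends, and the sample sizes, come from pairs of rates solved back to about 236 per group (17.3% v 8.65%, 24% v 13.9%) and about 267 (15.5% v 7.75%, 34% v 23.1%).

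| Assumed c | Share of effect left | Of 12 points | Power | Total N for 80%, readmissions | Total N for 80%, ED visits |
|---|---|---|---|---|---|
| 0% | 1.00 | 12.0 | 80% | 472 | 534 |
| 10% | 0.90 | 10.8 | 71–73% | 566–570 | 642–656 |
| 20% | 0.80 | 9.6 | 61–64% | 696–706 | 788–822 |
| 30% | 0.70 | 8.4 | 50–54% | 882–902 | 998–1060 |
| 50% | 0.50 | 6.0 | 29–33% | 1618–1688 | 1828–2024 |

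The power and N columns ignore clustering and the stepped-wedge layout, so they show direction and rough scale only.

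**5. Which outcomes this route reaches.** An ordinary home care order by an untrained case manager raises the home care referral rate in control cells. It does not raise Table 3's THRIVE-referral proportion. Readmissions and ED visits could move only through changed physician, nurse or case-manager behaviour.

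**The case against.** The strongest reply is that silence is being read as a defect. The article does not say that the flag, dashboard, champions or training began hospital-wide. Reminders at weeks 2, 4 and 6 fit inside an 8-week step, and activation dates are detail that a full protocol may hold. THRIVE visits, physician oversight and case conferences follow a case-manager referral, and untrained case managers cannot submit one. The flag prompts a THRIVE referral rather than ordinary home care. The fixed time effects are stated for use outcomes, not for referral, and leakage in periods 1 and 2 does not touch the comparison with baseline. Finally, (1 − c) follows directly from assuming c; it is no evidence that c exceeds zero.

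Most of this stands. A reader might infer that the components are not staggered, that control patients are exposed, or that the effect is diluted by a known amount. The document supports none of these: it is silent on timing, the full package is gated by referral, and c is purely assumed.

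The reply does not remove the shared-staff route. Physicians and home care nurses must be active in THRIVE for sequence 1, nothing assigns them to a sequence, and case managers share a workspace. The comparison with baseline avoids this leakage but is not randomised and is open to change over time. The stated contrast of THRIVE recipients with usual care (Current Usual Care, Aim 1, Table 3 footnote c) is no way out either. The (1 − c) result does not apply to it, and selection into referral adds bias of unknown direction.

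**Conclusion.** The point holds as a risk that the stated design leaves open, not as a demonstrated contamination. Control patients in periods 1 and 2 can be partly exposed through changed behaviour of shared staff, and the home care referral rate is the outcome most open to this. Under a time-adjusted comparison by assigned sequence and period, a leaked share c leaves (1 − c) of the effect. This assumes the same c in all control cells from step 1 onwards. With c = 0 nothing is lost; for any other value the size cannot be derived from the document. A reader might go further and expect the trial to miss a real benefit. That would need a value of c that the document does not supply, and for readmissions and ED use a large share would have to reach patients who receive neither the case conferences nor the extended physician oversight.

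**What to change.** 1. Show the flag, dashboard feedback and reminders only to case managers who have crossed over. Run the algorithm silently for the others, so that eligibility is logged identically in control periods.
2. Define each patient's condition by the case manager responsible for that patient and that case manager's randomised sequence and period, for all eligible patients, instead of by receipt of THRIVE. The rule for identifying the responsible case manager from the EHR should be fixed whoever files the referral.
3. Report home care referral by control case managers in periods 1 and 2 against baseline, as a descriptive check on leakage.
4. State when the shared physician and home care nurse training began, and interpret the randomised contrast as the effect of activating case managers given that training.

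Moving the shared training ahead of baseline would not help. Control cells would still carry c, the estimate would still be (1 − c) of the effect, and the check in part 3 would lose its clean reference.

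The cost is minor EHR configuration, some protocol wording and a narrower description of the effect; no patients or staff are added. If rollout is already complete, part 1 is too late, but parts 2 to 4 can still be done from EHR data and the study's own training records.

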### Evaluation

#### Aim 1

Aim 1 is to examine referral patterns, 30-day readmission, and 30-day ED use patterns for participants who receive THRIVE support services compared to those receiving usual care.

##### Outcomes and Measures

The primary outcome includes the referral rate to home care made by CMs compared to baseline and the nonrandomized cluster. The secondary outcomes are 30-day readmissions and ED visits. Additional covariate data at the patient (eg, demographics and comorbidities) and unit levels (eg, type of unit and discharging team or provider) will be collected from analyses. For THRIVE participants, these outcomes will be assessed from the date of hospitalization, which resulted in a referral to THRIVE. For the usual care group, we will identify all readmissions and ED visits occurring after the first index hospitalization identified in the EHR for the calendar year of the study. Outcome measures, guiding framework, data sources, collection, and timing are described in Table 3.

**Table 3 table3:** Summary of outcomes, measures, data sources, collection method, and timing.

Construct and framework					Design		Method of collection			Timing	
**Aim 1: Examine referral patterns, 30-day readmission, and ED^a^ use patterns for participants who receive THRIVE support services compared to those receiving usual care**											
	THRIVE referrals^b^ 30-day readmissions^c^ 30-day ED visits^c^ Primary care visit within 30 days of discharge^c^ Specialty care visit within 30 days of discharge^c^			Stepped wedge cluster randomized controlled trial		Electronic health record			Baseline and at the study end		
**Aim 2: Evaluate the implementation of the THRIVE clinical pathway, including fidelity, feasibility, appropriateness, and acceptability**											

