### THRIVE Eligibility Criteria

Individuals eligible for a THRIVE referral include (1) being Medicaid insured, dually enrolled in Medicaid and Medicare, or Medicaid eligible; (2) residing in Philadelphia; (3) having experienced a hospitalization at the study hospital for more than 24 hours with a planned discharge to home; (4) agreeing to home care at partner home care settings; and (5) being aged 18 years or older. If home care services are declined at any time following discharge, THRIVE services are also discontinued. If palliative or hospice services are ordered following discharge, THRIVE services will not be offered.

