	**Proctor implementation outcomes**										
		Acceptability^i^ Appropriateness^j^ Feasibility^k^	Mixed methods approach to determine the Proctor implementation outcomes					Survey and interviews with clinicians and administrators			8-week postintervention from the start of each sequence and at the study end
		Fidelity^l^	Retrospective chart review					Standardized THRIVE checklist			Monthly

^a^ED: emergency department.

^b^Proportion of THRIVE referrals of those who are THRIVE eligible.

^c^Proportion of THRIVE participants experiencing the outcome within 30 days of discharge compared to usual care group.

^d^Organizational commitment to addressing disparities.

^e^Relative advantage of THRIVE to patients, degree of fit with existing practice, competing demands, and bias.

^f^Structures outside of the hospital that affect patient care.

^g^Organizational values, culture embedding, and championing adaption.

^h^Organizational priorities and goals and readiness for change and culture or climate.

^i^How fair or reasonable THRIVE is deemed.

^j^To what extent THRIVE seems suitable.

^k^The practicality and ease of delivering THRIVE.

^l^Fidelity to THRIVE’s core components.

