##### Analysis

We will develop monthly reports to monitor the referral patterns to the THRIVE clinical pathway. The target estimate and effect measure is the time-adjusted difference in participant outcomes [53,54]. The analysis of use outcomes (eg, 30-day readmissions and ED use) will use a mixed effects negative binomial regression model with random effects for the medical team and fixed effects for time to account for the stepped wedge cluster randomized design. Sensitivity analyses may be performed using logistic regression for health service use based on the distribution of the data. We will also examine the stability of effect estimates using generalized estimation equations with small sample adjustment, given the study design [55].

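### The Aim 1 timing sentences start the outcome clock differently in the two groups and conflict with the 30-days-from-discharge rule in Table 3; followed literally, they favour THRIVE on readmission

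*Protocol article*

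**What the plan says.** All statements are in the protocol article.

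- **Outcome label** (Aim 1, Outcomes and Measures): "The secondary outcomes are 30-day readmissions and ED visits". This sentence does not say from when the 30 days run.
- **THRIVE group** (same paragraph): "For THRIVE participants, these outcomes will be assessed from the date of hospitalization, which resulted in a referral to THRIVE". The start is the hospitalization date. The sentence gives no end.
- **Usual-care group** (next sentence): "we will identify all readmissions and ED visits occurring after the first index hospitalization identified in the EHR". The start is after the index stay. This sentence gives no end either.
- **Table 3, footnote c**, attached to 30-day readmissions, 30-day ED visits and the two follow-up visit outcomes: "Proportion of THRIVE participants experiencing the outcome within 30 days of discharge compared to usual care group". The start is discharge and the end is day 30.
- **THRIVE Eligibility Criteria**: "having experienced a hospitalization at the study hospital for more than 24 hours with a planned discharge to home". Admission and discharge are therefore more than a day apart for every THRIVE-eligible patient.
- **Aim 1, Analysis**: the use outcomes "will use a mixed effects negative binomial regression model with random effects for the medical team and fixed effects for time".

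**The concern.** A 30-day outcome needs one start and one end, the same in both groups. Here the start is written by group: admission for THRIVE, after the stay for usual care. A patient cannot be readmitted while still in the index stay, so a clock started at admission spends its first days with no possibility of the event. The usual-care clock does not. The shortfall in time at risk falls on one group only, and for readmission it can act only in THRIVE's favour.

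The planned model would not remove this. Fixed effects for time and random effects for the medical team do not address a window defined by treatment group. In a count model, unequal time at risk goes straight into the rate ratio unless exposure is adjusted for.

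These outcomes matter. They are part of Hypothesis 1, the Sample Size section rests on them alone, and the Design and Randomization overview lists them among the primary outcomes, although Outcomes and Measures calls them secondary.

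**Working it through.** **1. The rules side by side**

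| Source | Group | Start | End in that text |
|---|---|---|---|
| Outcomes and Measures | THRIVE | date of hospitalization | none (outcome labelled 30-day) |
| Outcomes and Measures | usual care | after the index stay | none (outcome labelled 30-day) |
| Table 3, footnote c | THRIVE compared with usual care | discharge | 30 days |

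The THRIVE start conflicts with footnote c. The usual-care start can be squared with it, but that sentence omits the limit.

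**2. Inputs for the size of the effect**

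- 30-day readmission risk p = 0.24 in both groups, so no treatment effect. This is the Introduction's background figure for Medicaid-insured adults aged 45-64. It is not stated to be the trial's planning rate.
- Length of index stay L = 3, 5 or 7 days. Assumption; the article gives only the minimum of more than 24 hours.
- Weibull time to readmission after discharge, shape k = 1.0 (constant hazard) to 0.7 (early events more frequent). Assumption.
- A 30-day limit in both groups, as the outcome label implies.

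The article has no figure of its own to reproduce on this point. Its sample sizes (236 and 267 per group) come without a control rate or effect, so they cannot be checked, and the result below does not depend on them.

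**3. Formula**

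The risk by day t after discharge is 1 − (1 − p)^((t/30)^k). Counting 30 days from admission leaves t = 30 − L days after discharge, so the THRIVE group shows

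1 − 0.76^(((30 − L)/30)^k), against 0.24 in usual care.

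**4. Numbers**

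For L = 5, k = 1.0: 25/30 = 0.833, and 1 − 0.76^0.833 = 0.204. Difference: 0.240 − 0.204 = 0.036.

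For L = 5, k = 0.7: 0.833^0.7 = 0.880, and 1 − 0.76^0.880 = 0.215. Difference: 0.025.

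| Stay L | THRIVE, k = 1.0 | THRIVE, k = 0.7 | Usual care | Spurious fall (points) |
|---|---|---|---|---|
| 3 days | 21.9% | 22.5% | 24% | 1.5 to 2.1 |
| 5 days | 20.4% | 21.5% | 24% | 2.5 to 3.6 |
| 7 days | 19.0% | 20.4% | 24% | 3.6 to 5.0 |

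For 5 days this is a relative fall of 11% to 15%. On the count scale with a constant rate and no exposure adjustment, the rate ratio would be 25/30 = 0.83 with no true effect.

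**5. Effect on the test**

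Two-sided two-proportion z-test at .05, 267 per group, patients treated as independent, k = 1.0. Let d be the difference, s0 the standard error under the pooled proportion and s1 the unpooled one. The rejection probability is 1 − Φ((1.96·s0 − d)/s1) + Φ((−1.96·s0 − d)/s1). It is about 17% for a 5-day stay and 29% for a 7-day stay, against 5% when both groups share one window. Clustering is ignored, so these figures illustrate the direction and rough size rather than the trial's actual error rate.

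**The case against.** The strongest reply is that the article already contains one common rule. Aim 1 speaks of 30-day readmission and 30-day ED use, the paragraph at issue carries the same label and sends the reader to Table 3 for measures and timing, and footnote c there is clear. The two group sentences may be meant only to identify the index stay: the one that produced the referral, or the first of the year. An analyst working from Table 3 would then use the same window in both groups and no bias would arise. This is plausible, and it is why the false difference must be stated as conditional. It does not remove the conflict: the THRIVE sentence says outcomes are assessed from the hospitalization date, and footnote c says from discharge.

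Three stronger readings are tempting, and the article does not support them.

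- **That a spurious difference will appear.** It appears only if the literal wording, and not footnote c, governs the data extraction.
- **That usual care is followed without limit while THRIVE is stopped at 30 days.** With the same assumptions, usual care left open to 90 days would show 45% to 56% against 24%. That takes the 30-day limit from elsewhere for one group and withholds it from the other. Neither sentence states an end, and the 30-day label covers both groups. The figure is a worst case, not the expected consequence.
- **That ED visits are biased in a known direction.** Lost days would lower the THRIVE count, while counting the arrival that led to the index stay would raise it. Nothing in the article says that arrival would be counted.

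It is also fair that length of stay, hazard shape and the 24% risk are not trial-specific inputs. They limit what can be said about size; the direction for readmission under the literal reading does not depend on them.

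**Conclusion.** The point stands as a contradiction between stated rules, with a conditional bias. The Aim 1 timing sentences and footnote c of Table 3 give different starts for the same outcomes, and the difference runs along treatment group. This is more than detail left to an analysis plan, because the article states the rules and they disagree.

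If the sentences are followed as written with a 30-day limit in both groups, readmission is biased towards THRIVE by about 1.5 to 5.0 percentage points for stays of 3 to 7 days. If footnote c is followed, this bias is zero. The article does not settle which applies. The size rests on the assumed 24% risk, the assumed lengths of stay and a Weibull shape of 0.7 to 1.0. For ED visits the direction is uncertain.

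**What to change.** In Aim 1, Outcomes and Measures, replace the timing in both sentences with footnote c's rule for both groups: readmissions and ED visits within 30 days after discharge from the index stay. State that the index stay itself and any ED visit leading to it are not counted. Keep same-day returns after discharge, and treat them the same way in both groups; starting the count on the day after discharge would drop them and goes beyond footnote c. How the index stay is identified in each group can remain in a separate sentence, so that it is not read as a start of follow-up.

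The cost is a short text change, repeated in the data extraction specification. It uses the same electronic health record source, needs no new data and leaves the sample size as it is. It should be settled before outcomes are extracted and compared.

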### Design and Randomization

#### Overview

This is a prospective single-site type 1 hybrid effectiveness-implementation pragmatic stepped wedge cluster RCT. Our stepped wedge design will include a sequential randomized rollout of the intervention to case managers at PAH in 3 steps, and data collection will occur over 18 months. This mixed methods (quantitative and qualitative) study design involves simultaneous collection and analysis of quantitative and qualitative data, giving priority weight to the quantitative data to evaluate program referrals, outcomes, and program fidelity, while qualitative data will evaluate the process through detailed descriptions of perspectives of barriers and facilitators faced by health care providers in implementing the THRIVE intervention [51]. This study includes qualitative interviews and surveys of clinicians and administrators to assess their perspectives on appropriateness, feasibility, and acceptability of THRIVE. Nesting the qualitative interviews within an RCT of the THRIVE intervention will allow us to determine whether the intervention improved primary outcomes (referrals to home care, 30-day readmission, ED use, and connection to primary care providers) and to identify professional and organizational barriers to implementation. Combining these insights with effectiveness outcome data will allow consideration for meaningful contextual factors that are considered critical to the implementation of THRIVE and subsequent outcomes.

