## Results

This project was funded in January 2023. We received IRB approval on March 10, 2023. Data collection will occur from March 2023 to July 2024. Results are expected to be published in 2025.

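### The usual-care index window is an undefined calendar year and is not limited to the control phases, so it can admit post-crossover patients as controls

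*Protocol article*

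**What the plan says.** The article describes the comparator in two places that do not match.

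- **Current Usual Care** ties it to the wedge: "The current usual care will serve as the control condition that patients will receive during the control phases of the design".
- **Outcomes and Measures (Aim 1)** gives the only rule for picking a usual-care patient's index stay: "the first index hospitalization identified in the EHR for the calendar year of the study". It names no year and does not mention control periods. THRIVE patients are indexed differently, at the stay that led to their referral.

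The timetable comes from three places. Results states: "Data collection will occur from March 2023 to July 2024". The design Overview says that "data collection will occur over 18 months". Randomization and Table 2 give the case-manager groups ("4 in the first group, 4 in the second, and 5 in the third"), a 3-month baseline and the step length: "At 8-week intervals, the remaining case managers will be trained in the THRIVE intervention". In Table 2 all 13 case managers are on THRIVE from enrollment period 3 onward.

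**The concern.** A study that runs from March 2023 to July 2024 touches two calendar years, so the stated window has no definite meaning. Whichever year is chosen, it does not coincide with the control phases.

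This matters because of who is labelled usual care after a case manager has crossed over. Implementation Strategies foresees eligible patients who are not referred, and THRIVE Eligibility Criteria makes acceptance of home care a condition of entry. Post-crossover patients without THRIVE are therefore those a trained case manager passed over or who declined home care. Setting them against THRIVE recipients compares receipt with non-receipt. It is not the contrast between crossed-over and not-yet-crossed-over case managers that the stepped-wedge schedule creates, and fixed effects for time do not remove that selection. Readmission and ED use, the two outcomes on which the sample size rests, are the ones affected.

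The first-stay rule adds a smaller problem. If the year means 2023 from 1 January, a patient admitted before the trial began is indexed there, and any later control-phase stay is not used.

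**Working it through.** The protocol states no figure for the share of control time, so there is nothing of its own to reproduce. The check counts case-manager-weeks (CM-weeks) from Table 2.

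**Inputs.** 4, 4 and 5 case managers per sequence (Randomization); 3-month baseline, taken as 13 weeks; 8-week steps; data collection March 2023 to July 2024 (Results). Assumption: baseline starts in March 2023, on the 1st, 10th or 31st to show the range.

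**Control time.**
- Baseline, all 13 in control: 13 × 13 = 169
- Enrollment period 1, 9 in control: 9 × 8 = 72
- Enrollment period 2, 5 in control: 5 × 8 = 40
- Period 3 and follow-up: 0
- Total: 169 + 72 + 40 = 281 CM-weeks

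**End of control time.** 13 + 16 = 29 weeks after the start: 20 September 2023 for a 1 March start and 20 October 2023 for a 31 March start. None falls in 2024.

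**Calendar 2023.** The denominator is 13 × 365/7 = 678 CM-weeks. Time before baseline is 13 × days/7, and post-crossover time is the remainder.

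| Baseline start | Before baseline | Table 2 control | Post-crossover |
|---|---|---|---|
| 1 March | 13 × 59/7 = 110 (16%) | 281 (41%) | 287 (42%) |
| 10 March | 13 × 68/7 = 126 (19%) | 281 (41%) | 271 (40%) |
| 31 March | 13 × 89/7 = 165 (24%) | 281 (41%) | 232 (34%) |

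**Other readings of the window.**
- Start to 31 December 2023: 281/568 to 281/513 = 49-55% control, so 45-51% post-crossover.
- Twelve months from the start: 281/678 = 41% control, 59% post-crossover.
- Start to 31 July 2024: 281/964 to 281/908 = 29-31% control, 69-71% post-crossover.
- Eighteen months from the start: 281/1018 = 28% control, 72% post-crossover.
- Calendar 2024: 0% control.

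**Sensitivity to the assumption.** If March 2023 was instead the first crossover, with baseline before it, calendar 2023 is 33-41% control and 59-67% post-crossover.

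No reading of the window coincides with the control phases.

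**The case against.** The strongest reply is that Current Usual Care already places usual care in the control phases, so the later sentence may only fix the stay from which outcomes are counted within a group defined elsewhere. On that view the plan does not choose non-control time; it fails to repeat a restriction. This stands as a reading, and a reader should not infer that the authors deliberately replaced the control phases with a calendar year. It does not settle the matter. The data-collection section and the footnote to Table 3 describe the comparison by receipt of THRIVE, and whoever draws the EHR extract has only the calendar-year rule to follow.

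A reader might also infer that most of calendar 2023 is not control time, since 281/678 leaves 59% outside the Table 2 control cells. The documents do not support that. With a March baseline, 16-24% of the year precedes it, when no case manager at this hospital had been trained. Those discharges lie outside the periods of Table 2 but are untreated. Counting them with the control cells makes 2023 58-66% untreated. A post-crossover majority holds over the whole data-collection period, over 12 months from the start and in 2024, or in 2023 only if March was the first crossover.

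Three further limits stand.
- Referred patients leave the usual-care pool after crossover, so the post-crossover share of usual-care patients is probably below the CM-time share. No patient flow is given.
- A 2023 window contains every control-phase week. A control-phase stay is lost only for a patient with an earlier stay that year, and the number of such patients is unknown.
- Outcomes and Measures names the referral rate as primary, and this rule does not touch it. The design Overview, however, lists readmission and ED use among the primary outcomes.

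Exact extract dates may well be left to a fuller document. The point here is a rule that is stated and conflicts with another section.

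**Conclusion.** The point holds as an internal conflict with a real risk of bias. The calendar-year rule is undefined for a study spanning two years, and it is not limited to the control phases to which the protocol elsewhere ties usual care. Followed literally, it admits unreferred or declining post-crossover patients as controls for readmission and ED use, and it indexes the two groups by different rules.

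In CM-time, the post-crossover share is 34-42% of calendar 2023, about 70% of the whole data-collection period and 100% of 2024. These shares assume a March 2023 baseline start, a 13-week baseline and equal weight for each case manager's time. They indicate exposure to the problem; they do not estimate patient numbers or the size of any bias, neither of which the documents allow one to compute.

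**What to change.** Reconcile Current Usual Care with Outcomes and Measures before the EHR extract is drawn. Replace the calendar-year wording with a rule such as: usual-care index stays are eligible discharges under a case manager who has not yet crossed over, dated from the first day of baseline to the day before that case manager's crossover; unreferred post-crossover patients are not used as usual-care controls.

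The change is one sentence and a date filter linked to each discharge's case manager. The cost is a smaller pool: 281 CM-weeks, of which only 72 + 40 = 112 run alongside case managers who have already crossed over. No rate of eligible patients is given, so the yield against the 267 planned comparisons (Sample Size) must be checked.

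This cleans the comparator only; the THRIVE group stays defined by referral and acceptance of home care. An analysis that counts every eligible post-crossover discharge as intervention condition could be added. That is a separate choice, because it departs from the receipt-based comparison in Aim 1 and from the 267 + 267 basis of the sample size.
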